## I. Background

Antibiotic resistance is one of the three greatest threats to human health according to the World Health Organization [1]. Antibiotic-resistant bacteria and *Clostridium difficile* are responsible for 2.3 million infections and 37,000 deaths in the U.S. every year [2]. Antibiotics are one of the most commonly prescribed medications in nursing homes (NHs). Up to 40% of NH residents are colonized with antibiotic-resistant bacteria [3], and NHs play a critical role in the emergence and spread of antibiotic resistance and *C. difficile* in the communities they serve [4-6]. Antibiotics are prescribed to 65% of individuals who reside in a NH for  $\geq 6$  months [7]. Treatment of suspected urinary tract infection (UTI) accounts for nearly half of the antibiotic use in Wisconsin NHs [1]. However, there is compelling evidence that antibiotic prescribing patterns in NHs is sub-optimal [5]. Less than half of the antibiotics prescribed for UTI in Wisconsin NHs are justified [6], and improving the management of UTI in NHs has been identified as a major priority by experts in the field [7-9].

We along with our community partners have developed a toolkit of evidence-based practices for improving the management of UTIs in Wisconsin NHs (hereafter referred to as the Wisconsin UTI Improvement Toolkit). While use of the practices incorporated in the Wisconsin UTI Improvement Toolkit has resulted in notable improvements in the quality of antibiotic prescribing for the treatment of UTI in a number of studies [10-12], more limited effects have been observed in other studies despite employing similar improvement strategies [13-15]. Heterogeneity of effects across different settings is a problem commonly encountered with healthcare behavioral interventions and may be due to characteristics of the intervention, the setting into which it is being introduced, and the method of implementing the intervention in that setting [16]. There are a number of challenges to improving quality in NHs, including lack of improvement expertise [17] and high levels of staff turnover [18] to name a few. It is unrealistic to expect that these structural barriers will abate anytime soon. Consequently, it is critically important to identify effective strategies to overcome them if meaningful improvements in the quality of antibiotic prescribing in NHs are to be achieved.

## II. Study Objectives

*Our long-term objective is to improve the quality and safety of antibiotic prescribing in Wisconsin NHs.*

The objective of the current project, which is a critical step in the pursuit of our long-term objective, is to identify effective strategies for supporting the implementation of antibiotic stewardship interventions in NHs. We hypothesize that externally-facilitated implementation based on coaching and peer-to-peer learning will be associated with: (**hypothesis 1**) better adoption of the Wisconsin UTI Improvement Toolkit and (**hypothesis 2**) reduced rates of inappropriate antibiotic use as compared to a usual implementation approach that relies predominantly on internal improvement resources available in NHs. We base these hypotheses on studies demonstrating more effective uptake of evidence-based practices with coaching [19-22] and peer-to-peer learning [23-25] in other healthcare settings, particularly resource-limited settings. A preliminary analysis of qualitative data collected from another of the PI's research projects (Agency for Healthcare Research and Quality 1R18 HS022465-01) indicates that clinical coaching is helping champions in study NHs identify barriers to change and develop more effective strategies for overcoming these barriers.

The primary study objectives are to assess the overall impact of the UTI Improvement Toolkit on antibiotic utilization and determine the extent to which effects vary by the implementation approach employed. We will achieve these two objectives through the following specific aims:

**Specific Aim 1: Evaluate the impact of the Wisconsin UTI Improvement Toolkit on antibiotic prescribing for UTI in Wisconsin NHs.**

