|                                 |                                     |                                                                                                   |                                       |
|---------------------------------|-------------------------------------|---------------------------------------------------------------------------------------------------|---------------------------------------|
| Resident Level Outcomes         | Antibiotic measures (Effectiveness) | FQ-AS and FQ-DOT per 1,000 resident-days                                                          |                                       |
|                                 |                                     | % of AS for UTI meeting appropriateness criteria                                                  |                                       |
|                                 |                                     | % urine cultures positive for resistant bacteria                                                  |                                       |
|                                 |                                     | Number of positive Clostridium difficile tests                                             |                                       |
|                                 | Testing measures (Effectiveness)    | Urine cultures per 1,000 resident-days                                                            | Facility supplied                     |
|                                 |                                     | % of urine cultures meeting appropriateness criteria                                              |                                       |
|                                 | Safety measures                     | Hospital/ED transfers per 1,000 resident-days                                                     | Facility supplied                     |
|                                 |                                     | Resident deaths per 1,000 resident-days                                                           |                                       |
| Nursing Home Quality Indicators | Quality indicators (Effectiveness)  | Residents with UTI; Prevalence of UTI infection (only) and all infections                         | CHSRA/DHS Nursing Home Scorecard      |

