## E.2. Study Measures

### E.2.1. Primary Measures

- Urine culture orders per 1,000 resident-days.
- Antibiotic starts for treatment of suspected UTI per 1,000 resident-days.

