### E.2.2. Secondary Measures

- Days of therapy for treatment of suspected UTI per 1,000 resident-days.
- Fluoroquinolone antibiotic starts and days of therapy per 1000 resident-days.
- Percentage of antibiotic starts for UTI meeting Wisconsin appropriateness criteria.
- Percentage of urine cultures meeting Wisconsin appropriateness criteria.
- Percentage of urine cultures positive for resistant bacteria.
- Number of positive *clostridium difficile* tests.
- Number of transfers to hospitals or emergency departments per 1000 resident-days.
- Number of resident deaths per 1000 resident-days.

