#### **E.3.2. Secondary Outcome Measures**

Participating NHs will submit data on the number of urine cultures and antibiotic starts meeting Wisconsin appropriateness criteria [cite] via a web-based portal on a monthly basis. The Wisconsin appropriateness criteria [cite] require residents to either exhibit symptoms that localize to the urinary tract (e.g., dysuria, frequency) or systemic signs of infection (e.g., fever, hypotension, etc.) in the absence of another obvious source of infection.

The research team will obtain aggregate data on antibiotic prescriptions from the facility consultant pharmacy in order to determine days of antibiotic therapy per 1,000 resident-days as well as the number of fluoroquinolone starts and days of fluoroquinolone antibiotic therapy.

The research team will obtain aggregate data on urine culture results to determine the rates of urine culture resistance in study nursing homes. *Clostridium difficile* results at a facility level will be obtained in a similar manner.

Facilities will be asked to provide their aggregate resident transfer and mortality data on a monthly basis.

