##### **F.1. Overview**

A mixed methods evaluation structured around the RE-AIM framework (Reach, Effectiveness, Adoption, Implementation and Maintenance) [32] will be employed to compare the impact of the two implementation strategies using data submitted by facilities, surveys, interviews and observations. Statistical comparisons using generalized linear mixed models [33] will be employed to examine if differences in antibiotic utilization for treatment of UTI exist between NHs in the two study arms. Data from surveys, interviews and observations will be analyzed using a mixed-methods approach to ascertain the extent to which recommended toolkit practices have been implemented in study NHs.

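### Hypothesis 2 is about inappropriate antibiotic use, but no listed measure is the rate of inappropriate UTI starts and no between-arm test or interval for it is specified

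*Protocol*

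**What the plan says.** Section II states hypothesis 2 as a comparison between implementation strategies: external facilitation is expected to give "reduced rates of inappropriate antibiotic use as compared to a usual implementation approach".

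The measures that could bear on it are these:

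- E.2.1 (primary): "Antibiotic starts for treatment of suspected UTI per 1,000 resident-days". This counts every UTI start, justified or not. The other primary measure, "Urine culture orders per 1,000 resident-days", concerns testing.
- E.2.2 (secondary): "Percentage of antibiotic starts for UTI meeting Wisconsin appropriateness criteria". The E.1 table lists the same quantity, again as a percentage. The remaining antibiotic measures (days of therapy, fluoroquinolone use) do not classify appropriateness.

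For the arm comparison, F.1 says that mixed models will "examine if differences in antibiotic utilization for treatment of UTI exist between NHs in the two study arms". E.4 and F.5 extend the segmented regression, which is introduced for the two primary outcomes, with an arm covariate.

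On data, E.3.1 has facilities report urine cultures and antibiotic starts each month, and E.3.2 adds the "number of urine cultures and antibiotic starts meeting Wisconsin appropriateness criteria". Section III.B describes a toolkit meant to hold back testing and treatment in low-risk residents, so it acts on the number of starts.

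**The concern.** The hypothesised quantity is inappropriate use, and each listed measure captures only part of it.

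Total starts mix appropriate and inappropriate treatment. The toolkit could lower both: delayed treatment should remove unjustified starts, and its UTI-prevention module could remove justified ones. A fall in the total does not show which has happened.

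The percentage is conditional on a start having occurred. Starts are counted after randomisation, and their number is itself an outcome that the arms may change. An arm difference in the percentage, or the lack of one, therefore need not correspond to a difference in inappropriate use per resident-day.

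At stake is whether the trial reports an estimate with an interval for the quantity named in hypothesis 2, or leaves readers to infer it from two separate results.

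**Working it through.** **Inputs.** From E.4: a baseline UTI treatment rate of about 4.0 per 1,000 resident-days and a reduction of at least 15%. From the Background: less than half of UTI antibiotics are justified. The exact share is not given, so 45% is assumed, with 40% and 49% as a range.

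**The plan's own figure.** E.4 claims 90% power for the 15% fall. This can be neither reproduced nor refuted, because residents per home, months of observation, alpha and variance inflation are not stated. With 15 homes (20 less 25%), a two-sided alpha of 0.05 and a simple before-after Poisson contrast, power is 0.897 for 100 residents per home, 3 months before, 9 months after and no inflation. Over a wider grid (51 to 100 residents, several month splits, inflation 1 to 5) it runs from 0.176 to 0.999. The figure concerns total starts in all sites pooled, and nothing below depends on it.

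**Splitting the total.** Inappropriate rate = total rate × (1 − proportion appropriate). At baseline, 4.0 × 0.45 = 1.80 appropriate and 4.0 × 0.55 = 2.20 inappropriate. A 15% fall removes 0.60, leaving 3.40.

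| Case | Appropriate | Inappropriate | Total | % appropriate | Change in inappropriate |
|---|---|---|---|---|---|
| Baseline | 1.80 | 2.20 | 4.00 | 45.0 | – |
| (a) all avoided starts inappropriate | 1.80 | 1.60 | 3.40 | 52.9 | −27.3% |
| (b) proportional | 1.53 | 1.87 | 3.40 | 45.0 | −15.0% |
| (c) all avoided starts appropriate | 1.20 | 2.20 | 3.40 | 35.3 | 0% |

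The primary measure reads −15% in every row. In (b) the percentage does not move although inappropriate use falls by 15%.

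**Range.** At 40% appropriate, case (a) is 2.40 to 1.80 (−25.0%). At 49% it is 2.04 to 1.44 (−29.4%). Cases (b) and (c) stay at −15% and 0%.

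**What the two measures give jointly.** 3.40 × (1 − 0.529) = 1.60, 3.40 × (1 − 0.450) = 1.87 and 3.40 × (1 − 0.353) = 2.20. The point estimate is recoverable in all three cases. The interval is not. On the log scale the arm effect on the inappropriate rate is the sum of the effect on total starts and the effect on (1 − proportion appropriate). Its variance includes their covariance within facilities, which two separately fitted models do not supply.

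**Precision.** With independent Poisson counts and equal exposure before and after, z is proportional to |ln(r1/r0)| / √(1/r0 + 1/r1).

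- Total starts: 0.1625 / 0.7376 = 0.220.
- Inappropriate, case (a): 0.3185 / 1.0390 = 0.306, ratio 1.39.
- Inappropriate, case (b): 0.1625 / 0.9946 = 0.163, ratio 0.74.
- Inappropriate, case (c): ratio 0.

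The new outcome therefore carries no general gain in precision.

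**The case against.** A reader might infer that the trial cannot answer hypothesis 2 at all. The protocol does not support that. Both ingredients are listed measures, and together they separate the three cases. What is missing is a specified test and interval.

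Other points on the plan's side:

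- *Rate may mean proportion.* E.3.2 speaks of rates of urine culture resistance, and the matching E.2.2 measure is a percentage. On that reading the appropriateness percentage is the complement of the hypothesised quantity. F.4.2 and F.5 can also be read as comparing it between arms, since the E.1 table lists it under effectiveness. This weakens the charge of a plain contradiction. It does not remove the moving denominator: the percentage can stay flat while inappropriate use per resident-day falls.
- *Total starts fit the primary objective.* Section II frames that objective as antibiotic utilisation. This stands, and the primary measures need no change.
- *An analysis plan could derive the rate.* It could. But the protocol itself sets both the hypothesis and the list of measures, and the two do not meet.
- *Case (c) is unlikely*, because the toolkit targets low-risk residents, and it would show as a fall in the percentage. This is fair. Case (b) is the more relevant one, because prevention and delayed treatment may act together.
- *Facilities classify appropriateness themselves*, and the toolkit standardises resident assessment. Coaching could move starts from inappropriate to appropriate through recording alone. This is the strongest point against relying on the new rate by itself. The existing percentage shares the weakness; total starts are less exposed.

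**Conclusion.** The point holds as a mismatch between a stated hypothesis and the measures and arm analysis meant to address it. It is worth an amendment, but it is not a failure of the design. A 15% fall in total starts fits anything from no change to a fall of about 27% in inappropriate starts (25% to 29% over the assumed 40% to 49% baseline). In the proportional case the percentage shows nothing.

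The figures rest on the protocol's 4.0 baseline rate and 15% effect and on an assumed share appropriate. E.4 states the 15% for a pooled before-after change. It is used here as an illustration, and the same arithmetic applies to an arm difference of that size. The argument concerns which quantity is estimated. It makes no claim of better power, since the z ratio against total starts is about 1.39, 0.74 or 0 depending on which starts are avoided.

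**What to change.** - In E.2.2, add a secondary measure: antibiotic starts for suspected UTI that do not meet the Wisconsin criteria, per 1,000 resident-days, calculated as total starts minus starts meeting the criteria.
- In E.4 and F.5, name it as the outcome that addresses hypothesis 2, analysed with the same Poisson model, a resident-days offset and the arm terms, and reported with a confidence interval.
- Report appropriate starts per 1,000 resident-days alongside. If inappropriate starts fall while appropriate starts rise and the total stays flat, reclassification is a likely explanation. State that the result is to be read together with total starts for this reason.
- Keep the primary measures and the percentages as they are. A parallel rate for urine cultures is optional, because hypothesis 2 concerns antibiotics only.

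The cost is one derived variable and a few sentences. Both counts are already submitted monthly, and resident-days are needed for the primary rates, so no new data collection is required. If the sponsor does not want the added outcome, hypothesis 2 could instead be reworded to total UTI antibiotic use, but the trial would then no longer set out to test the effect on inappropriate use.

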## **Specific Aim 2: Assess the influence of external facilitation on the adoption and the effects of the Wisconsin UTI Improvement Toolkit in Wisconsin NHs.**

At project conclusion, we will have (1) assessed the effects of externally-facilitated implementation on the adoption of evidence-based antibiotic stewardship practices in Wisconsin NHs, and (2) determined the key facilitators and barriers associated with the two implementation approaches employed.

### **III. Study Methods**

#### **A. Overall Study Design and plan**

We will introduce the Wisconsin UTI Improvement Toolkit (see Section III.B. Wisconsin UTI Improvement Toolkit) in 20 Wisconsin NHs and assess its impact on antibiotic utilization using segmented regression. Two different implementation strategies (see Section III.C. Study Arms) will be employed during the introduction of the Wisconsin UTI Improvement Toolkit in study NHs using a hybrid type 2 effectiveness-implementation study design in which half of the NHs will be randomized to usual (internally-driven) implementation with the other half randomized to externally-facilitated implementation based on coaching and peer-to-peer learning. The effects of the two implementation approaches will be assessed using a mixed methods approach.

#### **B. Wisconsin UTI Improvement Toolkit**

The PI ([name]) has worked with academic, community and public partners in Wisconsin to develop a multi-component toolkit to improve the management of UTIs in NHs. The WI Healthcare Associated Infections (HAI) in Long term care (LTC) UTI toolkit was developed through a rigorous review of published theory and evidence [7] with input from frontline clinicians who practice in Wisconsin NHs and is structured around a UTI management framework developed by the PI [31]. The toolkit targets three major nursing staff and provider behaviors: (a) standardization of the assessment of the resident experiencing a change-in-condition; (b) implementation of delayed testing and treatment of residents experiencing a low-risk change-in-condition; and (c) appropriate selection of antibiotics (drug, dose, duration) in those residents where the likelihood of UTI is high. Education, communication, and decision-support tools have been developed in order to achieve improvements in each of these behavioral domains, and the toolkit also includes recommended practices to help prevent UTIs as well as process and outcome tracking tools designed to help staff in NHs assess implementation progress. Further details about the UTI toolkit are provided in the Appendix.

#### **C. Study Arms**

##### **C.1. Control Arm: Internally-driven implementation**

Study NHs randomized to the control arm will participate in kickoff meetings introducing the different UTI toolkit components. The meeting will also cover topics on how to assemble a change team, how to use the different tools in the UTI toolkit, and how to track process and outcome measures to monitor progress. NHs assigned to the control arm will have access to a web-based data tracking tool that will allow them to trend a number of study outcomes (e.g., number of monthly urine cultures and UTI treatment events) in their facility over time. Instructions and educational tools will be made available as an online resource but otherwise NHs in the control arm will be expected to implement the Wisconsin UTI Improvement Toolkit using existing internal resources.

##### **C.2. Intervention Arm: Externally-facilitated implementation**

NHs randomized to the externally-facilitated arm will attend the same kickoff meetings and have access to the same online resources as the control arm but will also be assigned a clinical coach and will have the opportunity to participate in a series of hosted peer-to-peer learning opportunities. The clinical coach will meet regularly with NH staff to guide the facility through implementation of the Wisconsin UTI Improvement Toolkit. Coach supports will occur during a site visit and individual coaching calls.

### **C.2.1. Site Visit**

At the site visit, the coach will review the current UTI diagnosis and management-related workflows and work with SNF staff to identify opportunities to integrate different aspects of the Wisconsin UTI Improvement Toolkit into these existing workflows.

### **C.2.2. Individual Coaching Calls**

Following the site visits, the coach will conduct bi-weekly phone calls with staff in study NHs. These calls will focus on a number of topics, including:

- a) Establishing a change team;
- b) Identification of barriers and facilitators of change;
- c) Implementation of changes to support the ongoing integration of the toolkit practices into facility workflows;
- d) Review and interpretation of primary outcomes feedback reports;
- e) Identification and prioritization of future change efforts;
- f) Development of a plan to sustain improvement efforts following completion of the study.

### **C.2.3. Peer-to-Peer Learning Meetings**

The research team will host a series of learning meetings during which champions in intervention NHs will be encouraged to discuss successes/challenges and share ideas and strategies they employed to implement the toolkit. Participants will also be encouraged to collaborate with their peers in other facilities outside the formal peer-to-peer meetings.

### **C.2.4. Enhanced Feedback Reports**

Intervention NHs will be able to track their data using the web-based tracking tool that will be accessible by the control NHs. However, the feedback reports made available to intervention NHs will include information on the performance of other participating NHs (in aggregate) allowing the intervention NHs to trend their own data and benchmark themselves against their peers.

